##### **Definition of outcome measure (including trial periods)**

The fatigue and physical disability outcomes are continuous scores defined separately at weeks 12, 24, and 52. These are the primary outcomes.

Fatigue will be measured by the Likert scores of the CFQ (possible range 0 to 33).

Physical disability will be measured by the continuous scale of the SF36-PF (possible range 0 to 100).

##### 

**Descriptive statistics for outcome measures** The distributions of the Likert Chalder fatigue scores will be presented in frequency histograms both overall and by intervention at each assessment point (baseline, weeks 12, 24, and 52). The distribution of the SF-36 physical function subscale score will also be presented in histograms both overall and by intervention at each assessment point. It is anticipated that the distributions of the Likert Chalder fatigue score and the SF-36 physical function subscale score will be approximately normally distributed. Summary statistics (minimum, maximum, mean and standard deviation, median and inter-quartile range) will be tabulated and the response profiles plotted for each continuous score both overall and by intervention at each assessment point. The response profiles over time will also be plotted by outcome and intervention.

The mean scores (Likert Chalder fatigue scores and SF-36 physical function subscale scores) within each main therapist’s caseload will be calculated by therapy (APT, CBT and GET). These means will be plotted to investigate the level of variability in participant outcomes between therapists and to examine the distribution of these summary statistics (that is, whether they are normally distributed or skewed). Differences in the mean scores within each main doctor’s caseload will also be calculated and similar plots based on these presented.

##### 

**Primary analysis (including method of analysis)** The primary analysis addressing primary objectives (1) to (5) and secondary objectives (1) and (3) will be based on the principle of intention-to-treat. If missing data are estimated using multiple imputation this analysis will be based on the intention-to-treat sample (see Trial Samples); if missing data are estimated via prorating and maximum likelihood, the analysis will be based on the available-case sample (see Trial Samples) and will exclude any participants with no follow-up data in a ‘modified ITT’ analysis. The primary outcomes of fatigue and physical disability will be analysed separately using two mixed-effects linear regressions, each including participant as a random intercept and investigating adding a random slope on time. Time (investigating the possibility of linearising across 12, 24 and 52 weeks), the time-by-intervention interaction, baseline CFQ Likert score, baseline SF-36 physical function score and the design factors (that is, centre, CDC criteria, London criteria and current depressive disorder) will be included as fixed effects. Primary interest will be in the fixed contrasts specified in Method for Handling Multiple Comparisons and Multiplicity section at 52 weeks. The statistical models used in the analysis will be reported in full.

##### 

**Clinical importance of the mean differences in primary outcomes at 52 weeks** This will be judged by reference to the trial sample SDs at baseline in this trial supported by estimates from other sources. Specifically, a difference between means of two intervention groups, at 52 weeks, of 0.3 SD will be regarded as of minimal clinical importance (a MCID) and of 0.5 SD as a clinically useful difference. From published literature on these scales these differences can be translated into 5 points on the SF-36PF, and 1.2 points on the CFQ, for minimal clinical importance and 8 points on the SF-36PF, and 2.0 points on the CFQ, for clinically useful.

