##### **Sample size calculation taken from the protocol (v5.2)**

The following is quoted from the PACE trial protocol (v5.2) (see also [13]) and describes sample size estimation based on percentages responding to the trial interventions. The primary outcomes were changed subsequently to measures on continuous scales.

At one year we assume that 60% will respond with CBT, 50% with GET, 25% with APT, and 10% with SSMC. The existing evidence suggests that at one-year follow-up, 50 to 63% of participants with CFS/ME had a positive outcome, by intention to treat, in the three RCTs of rehabilitative CBT [39-41] with 69% improved after an educational rehabilitation that closely resembled CBT [44]. This compares with 18 to 63% improved in the two RCTs of GET [42,43] and 47% improvement in a clinical audit of GET [45]. For usual medical care 6 to 17% improved by one year in two RCTs [40,41]. There are no previous RCTs of APT to guide us, but we estimate that APT will be at least as effective as the control therapy of relaxation and flexibility used in previous RCTs, with 26 to 27% improved on primary outcomes [39,43].

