##### **Withdrawals from the trial and losses to follow-up**

The decision to withdraw a participant from follow-up within the trial is made only when the participant withdraws their consent to research follow-up. All reasonable attempts are made to continue to follow up all participants, including those that withdraw from intervention.

For the purposes of analysis, losses to follow-up are those missing all primary outcome scale data at all follow-up assessments, those missing all primary outcome scale data at weeks 24 and 52, or those missing all primary outcome scale data at week 52.

The numbers of withdrawals and losses to follow-up will be reported (see Comparisons of Losses to Follow-Up).

#### **
*Statistical considerations*
**

##### 

**Stratification in the analysis** The primary analysis of therapy effect will be adjusted by the factors used for stratification at randomisation (that is, centre, CDC criteria, London criteria and current depressive disorder) [12,49] and by the baseline assessment of the outcome variable.

##### 

**Method for handling centre effects** The PACE trial was designed with variation in participant outcomes between centres rather than between doctors or therapists in mind. For the primary analysis to be consistent with the trial design, the primary method for handling contextual variation in the analysis of therapy effects will be to include centre as a fixed covariate. The centre that randomises the largest number of participants will be the reference category. The centre assigned to each participant will be based on the participant’s centre at randomisation. Consideration will also be given to including centre as a random effect [50].

##### 

**Method for handling other clustering effects** Outcomes at weeks 12, 24 and 52 are nested within participants. The primary method for handling clustering associated with repeated measurements will be to fit a cluster-specific random effects model [51-53] including the participant as a random intercept, and investigating the addition of a random slope over time. Where therapy effects cannot be interpreted as population-averaged effects because outcomes are binary, a population-average (GEE) model will also be fitted.

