The overall probability of falsely claiming a statistically significant result increases when multiple significance tests (or equally CIs) are interpreted simultaneously. Multiplicity considerations arise in this trial from the presence of (i) multiple outcomes, (ii) multiple intervention comparisons, and (iii) multiple analyses.

The strategy for adjusting, presenting and interpreting the results is set out below.

Multiplicity adjustments will be made as follows:

1. The following five comparisons will be made using two-sided hypothesis tests (alpha = 0.05) at 52 weeks: APT versus SSMC, CBT versus SSMC, GET versus SSMC, CBT versus APT, GET versus APT.

For the co-primary outcomes, fatigue and disability, and for the secondary outcome, the participant-rated CGI, *P*-values will be presented unadjusted for multiplicity.

2. In addition Bonferroni adjustment (0.05/5) will be applied separately to each of the three outcomes to control the outcome-wise type I error rate at 5%.

3. No adjustment will be made for any sensitivity analysis as their purpose is to increase confidence in the results obtained from the analysis nominated as primary [26].

4. No adjustment will be made within the principal paper(s) for other analyses including those for safety, secondary outcomes (except the CGI) [26], and health economics.

Presentation will occur as follows:

1. All analyses undertaken will be reported as far as practical (regardless of statistical significance) [65].

2. Estimated effects will be presented with unadjusted 2-sided 95% CIs and *P*-values.

3. *P*-values adjusted for multiplicity will also be presented and explained.

Interpretation will be done as indicated below:

1. Marginal interpretation of the results will be of primary interest and will be based on the size and precision of the observed differences between interventions with reference to point estimates and unadjusted 95% CIs.

2. Intervention recommendations will also take into consideration the consistency of effects

a. across any supportive intervention contrasts,

b. across sensitivity analyses, primary outcomes and time points,

c. across efficacy, safety and cost analyses, and

d. with the results of previous studies, and clinical and consumer opinions.

##### 

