##### **Baseline adjustment**

By design factors only

Not applicable

By design factors and additional factors

This is the primary analysis.

##### 

**Model assumption checks** The following assumptions will be checked:

1. Independence of residuals will be checked using the supportive analyses described in Method for Handling Other Clustering Effects section. ICC and within-cluster variance estimates will be reported.

2. Distribution of residuals and random effects will be checked visually using Q-Q plots and histograms of the residuals and by plotting the between-participant variation in participant outcomes and where appropriate the between-centre, the within-doctor but between-interventions, and the between-therapist variation in participant outcomes. Deviations from a Normal distribution would indicate a violation of model assumptions. In this event an alternative approach to the analysis would be investigated.

3. Equal variance of residuals will be checked visually using plots of the standardised residuals against the predicted values.

4. Absence of an intervention-by-centre interaction will be checked in the primary analysis by including fixed contrasts for the intervention-by-centre interaction.

Checks will be made for extreme outliers and points with high leverage. In the event that these are found, the analysis will be reported with and without these observations together with any relevant details.

##### 

**Other analyses supporting the primary analysis** A number of sensitivity analyses will be employed to examine the robustness of the conclusions of the primary analysis to:

1. Categorical responder/improver analysis.

Clinically significant improvement will be taken as a CGI participant score of 1 (very much improved) or 2 (much improved). CGI (P) scores of 3 (a little improved), 4 (no change) and 5 (a little worse) will be considered as non-improvement. CGI (P) scores of 6 (much worse) and 7 (very much worse) will be considered as deterioration. The primary analyses will be repeated replacing the primary outcomes with the CGI (P) (response versus no response versus deterioration) and using mixed-effects logistic regression.

2. Methods for handling missing data.

The primary analysis will be repeated assuming data are missing not at random (MNAR) as described in Method for Handling Dropouts and Missing Data section.

3. Choice of sample.

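### The primary model defaults to a participant random intercept and gives no rule for adding the random slope, so the covariance behind the week-52 confidence intervals is left open

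*SAP article*

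**What the plan says.** The section on the primary analysis of fatigue and disability fits one mixed-effects linear regression per outcome, "each including participant as a random intercept and investigating adding a random slope on time". The section on other clustering effects says the same of repeated measurements in general: "including the participant as a random intercept, and investigating the addition of a random slope over time". The primary analysis of the secondary efficacy outcomes repeats the structure.

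The three visits are treated as separate outcomes ("The fatigue and physical disability outcomes are continuous scores defined separately at weeks 12, 24, and 52"), but inference is aimed at the last: "Primary interest will be in the fixed contrasts specified in Method for Handling Multiple Comparisons and Multiplicity section at 52 weeks". At that visit "five comparisons will be made using two-sided hypothesis tests (alpha = 0.05) at 52 weeks", and in addition "Bonferroni adjustment (0.05/5) will be applied separately to each of the three outcomes".

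Under model assumption checks, item 3 reads: "Equal variance of residuals will be checked visually using plots of the standardised residuals against the predicted values". It names no action if the check fails. The only stated consequence, an unspecified alternative approach, is attached to item 2, which concerns normality. Standard deviations are to be tabulated at each assessment, but nothing links them to the choice of model.

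**The concern.** A participant random intercept with one residual variance is a compound-symmetry model: one variance for all visits and one correlation for all pairs. The week-52 contrasts then borrow their standard error from weeks 12 and 24. If spread differs between visits, the interval at week 52 has the wrong width.

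The random slope is the plan's way out, but it is only to be investigated. No test, threshold or decision-maker is given. The covariance behind ten primary intervals (five contrasts on two outcomes) would therefore be settled after the data are seen. This matters because the multiplicity section rests interpretation mainly on the size and precision of the differences, read from unadjusted 95% intervals. Missing outcome scales are also to be handled by maximum likelihood within this model, so a wrong correlation pattern could mis-weight participants who miss week 52.

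No other provision covers the point. The heteroscedastic models in the clustering section concern care-provider clusters, not visits. The GEE model is for binary outcomes. No robust standard error is named for the two scores.

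**Working it through.** **Inputs from the SAP.** Visits at weeks 12, 24 and 52; contrasts at week 52; two-sided 5% tests; Bonferroni level 0.05/5 = 0.01; 600 planned and 641 randomised. The plan has no figure of its own for the covariance. Its sample size (135/(1 - 0.10) = 150 per arm, 4 x 150 = 600) was built on response percentages and does not depend on the covariance.

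**Assumed inputs.** The SAP gives no follow-up SDs or correlations. The SD ratios below are assumptions. So are the correlations: 0.7 (weeks 12-24), 0.6 (24-52) and 0.5 (12-52).

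**Random intercept alone.** With complete data and a separate mean for each arm at each visit, the fitted variance at every visit is the mean of the three visit variances. Hence

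model SE / true SE at week 52 = r = sqrt[ (v12 + v24 + v52) / (3 x v52) ].

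The actual error rate is 2 x [1 - Phi(1.960 r)] for a nominal 5% test and 2 x [1 - Phi(2.576 r)] for a nominal 1% test. For example, SDs 1:1.10:1.25 give mean variance (1 + 1.21 + 1.5625)/3 = 1.2575, so r = sqrt(1.2575/1.5625) = 0.897.

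**Random intercept plus slope.** This structure was fitted by maximum likelihood to the same assumed covariance matrices. The last column is the expected likelihood-ratio statistic for adding the slope with 600 participants.

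| SD at 12:24:52 | mean variance | v52 | r, intercept only | error at 5% / 1% | SE ratio with slope | LR statistic |
|---|---|---|---|---|---|---|
| 1:1:1 | 1.0000 | 1.0000 | 1.000 | 5.0% / 1.0% | 1.007 | 54 |
| 1:1.05:1.10 | 1.1042 | 1.2100 | 0.955 | 6.1% / 1.4% | 1.006 | 60 |
| 1:1.10:1.25 | 1.2575 | 1.5625 | 0.897 | 7.9% / 2.1% | 1.002 | 97 |
| 1:1.15:1.35 | 1.3817 | 1.8225 | 0.871 | 8.8% / 2.5% | 1.002 | 124 |
| 1.2:1.1:1.0 | 1.2167 | 1.0000 | 1.103 | 3.1% / 0.5% | 1.009 | 77 |
| 1:1.25:1.10 | 1.2575 | 1.2100 | 1.019 | 4.6% / 0.9% | 1.032 | 16 |

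The 5% cut-off for the likelihood-ratio test on 2 degrees of freedom is 5.99. The last row is a non-linear pattern, with spread peaking at week 24. A straight-line slope cannot follow it and leaves about 3%; a sharper peak would leave more.

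**Parameter count.** Random intercept: 2. Random intercept plus slope: 4 (two variances, one covariance, one residual). Unstructured 3x3: 3 variances + 3 covariances = 6. The increase over the default is 6 - 2 = 4.

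**The case against.** The strongest reply is that the plan does not commit to compound symmetry. The sentence that names the random intercept also provides for a slope, and the slope removes nearly all of the error where spread changes steadily. It would also be hard to miss. The expected test statistics of 60 to 124 in the growing-spread scenarios are far above 5.99, and decaying correlations alone give 54. A reader might infer that the plan forces equal variances, or that its tests run at 6% to 9% instead of 5%. The documents support neither. Those rates belong only to the branch where the slope is left out, and any ordinary investigation would probably adopt it.

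A reader might also infer that spread must grow. The entry limits on both scales restrict scores at entry, and the sizing states "At one year we assume that 60% will respond with CBT, 50% with GET, 25% with APT, and 10% with SSMC". But the limits say nothing about change between weeks 12 and 52, and the response rates are for one year only. Therapy runs over the first 23 weeks, so responders could have separated by week 24. Growth is plausible but not shown.

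SDs by visit will be tabulated, analysis decisions documented and the models reported in full, so a change in spread would be visible. Random-coefficient models are also an accepted choice for three visits.

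All of this stands, and it shrinks the point without removing it. Disclosure is not pre-specification: an analyst who kept the random intercept would still be within the plan. Condensation for publication does not explain the gap either, because the article says the plan is reproduced almost as approved.

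**Conclusion.** The concern holds as a gap in pre-specification, not as a demonstrated error in the intervals. The default structure implies equal variances and correlations, and the step that would relax it has no adoption rule. The variance check is not by visit and leads to no action.

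If the slope were not adopted, the week-52 standard errors would be about 4% to 13% too small for a week-52 SD of 1.10 to 1.35 times the week-12 SD, or about 10% too large for SDs falling as 1.2:1.1:1.0. With the slope, the error is about 1% or less for steady trends and about 3% for the non-linear pattern tried. These sizes rest on assumed SD ratios, complete data and visit-specific means; the figures with the slope also rest on the assumed correlations. The documents settle neither direction nor size. The recommendation does not depend on direction, because an unstructured covariance fits whichever way spread moves.

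**What to change.** In the primary analysis of fatigue and disability, and to match in the section on other clustering effects and for the continuous secondary efficacy outcomes, pre-specify categorical time with an unstructured 3x3 covariance for the three visits within participant.

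Name the fallback. If the unstructured model does not converge, or if time is fitted as continuous under the research visit window section, use random intercept plus random slope. Do not fall back to the random intercept alone.

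The cost is a change of SAP wording and one option in the Stata mixed command. Four more covariance parameters than the default are negligible with 641 randomised. The intervals may become slightly wider. A three-visit unstructured matrix does not carry over to continuous time, which is why that contingency needs its own stated structure.

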##### **Baseline adjustment**

By design factors only

Not applicable

By design factors and additional factors

This is the primary analysis.

##### 

**Model assumption checks** The following assumptions will be checked:

1. Independence of residuals will be checked using the supportive analyses described in Method for Handling Other Clustering Effects section. ICC and within-cluster variance estimates will be reported.

2. Distribution of residuals and random effects will be checked visually using Q-Q plots and histograms of the residuals and by plotting the between-participant variation in participant outcomes and where appropriate the between-centre, the within-doctor but between-interventions, and the between-therapist variation in participant outcomes. Deviations from a Normal distribution would indicate a violation of model assumptions. In this event an alternative approach to the analysis would be investigated.

3. Equal variance of residuals will be checked visually using plots of the standardised residuals against the predicted values.

4. Absence of an intervention-by-centre interaction will be checked in the primary analysis by including fixed contrasts for the intervention-by-centre interaction.

Checks will be made for extreme outliers and points with high leverage. In the event that these are found, the analysis will be reported with and without these observations together with any relevant details.

##### 

**Other analyses supporting the primary analysis** A number of sensitivity analyses will be employed to examine the robustness of the conclusions of the primary analysis to:

1. Categorical responder/improver analysis.

Clinically significant improvement will be taken as a CGI participant score of 1 (very much improved) or 2 (much improved). CGI (P) scores of 3 (a little improved), 4 (no change) and 5 (a little worse) will be considered as non-improvement. CGI (P) scores of 6 (much worse) and 7 (very much worse) will be considered as deterioration. The primary analyses will be repeated replacing the primary outcomes with the CGI (P) (response versus no response versus deterioration) and using mixed-effects logistic regression.

2. Methods for handling missing data.

The primary analysis will be repeated assuming data are missing not at random (MNAR) as described in Method for Handling Dropouts and Missing Data section.

3. Choice of sample.

A per-protocol analysis will be employed using the per-protocol sample to examine the robustness of the results of the primary analysis to departures from the intended randomised intervention or eligibility criteria.

##### 

**Additional analyses** The CBT versus GET contrast will be reported, recognising its exploratory status.

Secondary objective (2) (Do different interventions have differential effects on primary outcomes?) will be addressed by extracting fixed contrasts for the outcome-type-by-intervention interaction from a bivariate mixed-effects linear regression [51,72-74] fitted with fatigue and physical disability as joint outcomes, participant as a random effect (investigating adding a random slope on time), outcome-type (physical disability versus fatigue), intervention (all contrasts specified), time (investigating linearising this effect across 12, 24 and 52 weeks), the time-by-intervention interaction, the outcome-type-by-intervention interaction, baseline CFQ Likert score, baseline SF-36 physical function score and the design factors (that is, centre, CDC criteria, London criteria and current depressive disorder) as fixed effects. These contrasts directly estimate the differences in the intervention effects between the two primary outcomes.

#### **
*Analysis of secondary outcomes*
**

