**Questionnaires**						
Chalder fatigue	✓	✓	✓	✓	✓	✓
SF-36 physical functioning	✓	✓	✓	✓	✓	✓
Participant CGI		✓	✓	✓	✓	✓
Doctor CGI				✓	✓	✓
Therapist CGI			✓		✓	✓
Walking test	✓		✓	✓	✓	
Actigraphy	✓					
HADS	✓	✓	✓	✓	✓	
Self-efficacy	✓	✓	✓	✓	✓	
WSAS	✓	✓	✓	✓	✓	
SIQ^b^	✓	✓	✓	✓		
PHQ-15	✓	✓	✓	✓	✓	
Exercise and activity	✓	✓	✓	✓	✓	
Jenkins Sleep Scale	✓	✓	✓	✓	✓	
Step test	✓	✓	✓	✓	✓	
Borg Scale	✓	✓	✓	✓	✓	
Participant satisfaction			✓	✓		
SSMC/therapy adherence			✓	✓	✓	✓
EQ-5D	✓		✓	✓	✓	
CSRI	✓		✓	✓	✓	

^a^Baseline was conducted over two research visits prior to randomisation; ^b^The SIQ is now known as the Cognitive and Behavioural Questionnaire; ^c^The therapist and doctor data will be kept separate from the trial database and summarised by the Trial Manager (see Baseline Comparability of Randomised Groups); Note: CDC, Centers for Disease Control; CGI, clinical global impression; CSRI, client service receipt inventory; EQ-5D, Euroqol 5 dimensions; HADS, hospital anxiety and depression scale; PHQ15, physical health questionnaire 15; SF-36, short-form 36; SIQ, symptoms interpretation questionnaire; SSMC, standardised specialist medical care; WSAS, work and social adjustment scale.

In addition, details were recorded for i) training sessions, ii) therapist competency, iii) quality control checks of therapy sessions, and iv) homework compliance assessments that were made after every therapy session and that will be summarized as part of the general description of intended intervention policies.

Primary and secondary outcome variables will be derived from the follow-up data at each relevant time-point as follows.

Primary outcomes:

i) Fatigue total score (Likert scoring, higher scores indicate more fatigue).

ii) Physical disability total score (sum of 10 items multiplied by 5, lower scores indicate more disability).

Secondary outcomes are presented in Table 3.

**Table 3 T3:** Derivation of secondary outcomes

	**Secondary outcome**	**Derivation**
iii)	Serious deterioration	Absent/present - derived using the DMEC algorithm
iv)	Serious deterioration: Component 1	Absent/present - SF-36 physical function score diminishing by 20 or more points between baseline and any two consecutive assessment interviews
v)	Serious deterioration: Component 2	Absent/present - Participant-rated CGI change score of ‘much worse’ or ‘very much worse’ at two consecutive assessment interviews

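### As the two scores are defined, the contrast for secondary objective 2 adds the fatigue and disability benefits in unlike units, so it does not estimate a differential effect

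*SAP article*

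**What the plan says.** Under Additional analyses, in the part on the co-primary outcomes, the SAP addresses secondary objective 2 by "extracting fixed contrasts for the outcome-type-by-intervention interaction from a bivariate mixed-effects linear regression", with fatigue and physical disability as joint outcomes. It then says of the result: "These contrasts directly estimate the differences in the intervention effects between the two primary outcomes". No other analysis is planned for this objective.

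The scores are defined in two places. Baseline and outcome measures gives their directions: "Fatigue total score (Likert scoring, higher scores indicate more fatigue" and "Physical disability total score (sum of 10 items multiplied by 5, lower scores indicate more disability". Definition of outcome measure gives their ranges: "Fatigue will be measured by the Likert scores of the CFQ (possible range 0 to 33" and "Physical disability will be measured by the continuous scale of the SF36-PF (possible range 0 to 100".

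The only scaling of these outcomes by an SD is in the section on the clinical importance of mean differences, where "0.3 SD will be regarded as of minimal clinical importance (a MCID) and of 0.5 SD as a clinically useful difference". That section converts the smaller difference to "5 points on the SF-36PF, and 1.2 points on the CFQ, for minimal clinical importance", and the larger one to 8 and 2.0 points. This serves the interpretation of the separate analyses and is not tied to the joint model. Nowhere does the SAP say that either score is reversed, standardised or rescaled before the joint model is fitted.

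**The concern.** An interaction between outcome type and intervention is one effect minus the other. It measures a differential effect only if both outcomes point the same way and are in comparable units. Here a helpful therapy raises the SF-36PF and lowers the CFQ, so the subtraction turns into a sum. The units also differ about fourfold by the plan's own conversion.

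The contrast would then mostly reflect how much a therapy helps overall, weighted towards the SF-36PF. A reader who took it as the SAP describes it could conclude that a therapy acts differently on fatigue and disability when it helps both to the same degree. What is at stake is the answer to a pre-specified secondary objective.

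**Working it through.** **Inputs from the SAP.** Directions and ranges as quoted. Equally important differences: 0.3 SD = 5 SF-36PF points = 1.2 CFQ points; 0.5 SD = 8 SF-36PF points = 2.0 CFQ points. About 150 participants per arm (sample size section). A figure of 144 per arm comes from 641 randomised: 641/4 × 0.9 = 144.

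**Inputs not given.** The SDs and the correlation between the two scores. The SDs are inferred in the next step. The correlation is assumed to lie between 0 and −0.6.

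**The plan's own conversion.** For the CFQ, 1.2/0.3 = 4 and 2.0/0.5 = 4. For the SF-36PF, 5/0.3 = 16.7 and 8/0.5 = 16; with an SD of 16, 0.3 SD is 4.8, which rounds to 5. The stated points are thus reproduced with SDs of about 16 and 4.

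**Expected contrast under equal benefit.** Contrast = (SF-36PF effect) − (CFQ effect), where a benefit is positive on the first scale and negative on the second.

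| Equal benefit | Scores as defined | CFQ reversed only | Reversed and divided by SD |
|---|---|---|---|
| 0.5 SD (8; 2.0) | 8 − (−2.0) = 10 | 8 − 2.0 = 6 | 8/16 − 2.0/4 = 0 |
| 0.3 SD (5; 1.2) | 5 − (−1.2) = 6.2 | 5 − 1.2 = 3.8 | 5/16 − 1.2/4 = 0.01 (rounding) |

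Defining equal benefit in raw points does not help: a gain of d points on each gives d − (−d) = 2d. When there is a real effect, the raw contrast is zero only if both scores move by the same number of points in the same numeric direction, that is, if one outcome improves and the other worsens. Reversal without rescaling is not enough either, as the third column shows.

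**How often a test would be significant.** This is illustrative: one time point, no baseline adjustment, two-sided 5%. The variance of SF-36PF minus CFQ within a person is 16² + 4² − 2ρ(16)(4), and SE = √(2/n × variance).

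With n = 144 and ρ = −0.5: variance = 256 + 16 + 64 = 336; SE = √(2 × 336/144) = √4.67 = 2.16. For 10 points, z = 4.63 and the test is significant about 99.6% of the time. For 6.2 points, z = 2.87, about 82%.

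With n = 150 and the contrast taken as d × 16 + d × 4 = 20d:

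| Equal benefit d | Contrast | ρ = 0 | ρ = −0.3 | ρ = −0.6 |
|---|---|---|---|---|
| 0.5 SD | 10 | >99% | >99% | >99% |
| 0.3 SD | 6 | 88% | 84% | 80% |
| 0.2 SD | 4 | 56% | 50% | 46% |
| 0.1 SD | 2 | 18% | 16% | 15% |

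A simulation of 5,000 two-arm data sets per case (150 per arm, ρ = −0.5) agrees: mean contrast 10.0 with 99.7% significant at 0.5 SD, and 6.0 with 82% at 0.3 SD. With both scores aligned and divided by their SDs, about 5% were significant at every effect size.

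**Sensitivity to the SDs.** With SDs of 24 and 7, n = 144 and ρ = −0.5: variance = 576 + 49 + 168 = 793; SE = √(2 × 793/144) = 3.32. Then 10 points gives z = 3.01, about 85%, and 6.2 points gives z = 1.87, about 46%. Under these SDs the two raw effects are no longer exactly equal in SD units (8/24 = 0.33 and 2.0/7 = 0.29).

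**The case against.** The strongest reply is that the SAP is silent on the form in which the scores enter the model, rather than stating that raw scores are used. It cites methods references, not available here, and promises to report its models in full. This stands in part: use of the raw scores is inferred from the outcome definitions and the absence of any scaling step. But the paragraph lists the fixed effects one by one, the article says it reproduces the approved plan almost unchanged, and the claim that the contrasts directly estimate the difference is not true of the scores as defined. Nor does a bivariate model with separate parameters for each outcome repair it, because the contrast is still one raw effect minus the other.

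Other parts of the reply stand in full, and they limit what a reader might infer.

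- A reader might infer that the analysis will declare a differential effect every time a therapy helps both outcomes equally. Only the expected contrast is always non-zero. Significance depends on effect size, SDs and sample size. The SAP states no significance rule for this objective; its 5% level is tied to the five between-arm comparisons.
- A reader might infer that the contrast is wrong because it is not tied to week 52. Secondary objective 2 names no time point, and the section that puts primary interest at 52 weeks does not list this objective. A contrast over the whole follow-up is a legitimate choice.
- A reader might infer that shared covariate coefficients, or one participant effect shared by both outcomes, are errors in themselves. That depends on one reading of a short description. Shared covariate coefficients would mainly affect fit and precision and do not cause the sign and unit problem.

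**Conclusion.** The concern holds for the sign and the units. On the scores as the SAP defines them, the contrast for secondary objective 2 is a sum of benefits in unlike units: 10 points for equal 0.5 SD effects and 6.2 for equal 0.3 SD effects, where the standardised difference is zero apart from rounding. That rests on the SAP's own definitions and conversions, plus the absence of any stated reversal or scaling.

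The percentages are less firm. They rest on SDs of 16 and 4 inferred from the conversion and used as if they were follow-up SDs, on an assumed correlation, and on a single-time unadjusted comparison. Repeated measures and baseline adjustment would change the precision but would not bring the expected contrast to zero.

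A reader might infer that the trial's main results are compromised. They are not: fatigue and disability are analysed in separate models, and no primary estimate, interval or P-value is touched. This should be fixed, but it concerns one secondary objective.

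**What to change.** In Additional analyses, state that before the joint model is fitted one score is reversed so that both point the same way, and that each is divided by a pre-specified SD. The baseline SD, which the SAP already uses to judge clinical importance, is an obvious choice. The SD must be named in advance because it defines what equal benefit means, and entry limits on both scales may make the baseline spread narrower than the spread at follow-up. The outcome-type-by-intervention contrast is then extracted on that common scale and described as a difference in standardised effects.

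Two clarifications would sensibly go with this, though neither is the error: let the other fixed effects and the random and residual variances differ by outcome, and state the time point, or average over time, to which the contrast refers.

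The cost is SAP wording and model code. No data collection or primary analysis changes.
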